### Home-based physiotherapy intervention

The goal is to restore and increase the participant’s functional capacity, especially in activities of daily living, to prolong duration of living at home. One supervised physiotherapy session at the participant’s home lasts for 60 min, and takes place twice a week for 12 months. The participant has the same physiotherapist throughout the year. Physiotherapy is structured and progressive and consists of multicomponent exercises (Table 2). An individual physiotherapy plan is prepared by the physiotherapist in cooperation with the participant. The goal setting is done by using the Goal Attainment Scaling (GAS) method [29, 30]. Goals are evaluated and reported after 3, 6 and 12 months of therapy by the physiotherapist and the participant. The dates, duration, content (type, intensity, perceived exertion, and the number of sets and repetitions), and any adverse effects of each physiotherapy session are reported monthly by the physiotherapist.

**Table 2 Tab2:** Contents of home-based physiotherapy

	Warm-up	Strength exercises	Flexibility exercises	Balance exercises	Functional exercises
Modes of activities	Various activities	Orientation 2–3 weeks: based on the Otago exercise program [31] (5 leg muscle strengthening exercises with up to 4 levels of difficulty). Muscle strength, power and endurance periods, each 8 weeks, repeated twice during 12 months	Various flexibility exercises for large joints and the spine to enlarge the ROM	Otago [31] exercises (12 balance exercises with up to 4 levels of difficulty)	Flexibility, strength and balance exercises combined with IADL activities and walking outside
Intensity	Low to moderate	Moderate to vigorous (12–17 of RPE) [36]	Moderate	Challenges to the individual’s balance abilities	Challenges to the individual’s functional abilities
Progression	Changing intensity and activities according to physical condition	Using extra weights, increasing the level of difficulty	Changing activities	Selecting more advanced balance exercises (e.g. static, dynamic, dual task)	Selecting more advanced functional exercises
Frequency	2 times / week	2 times / week	2 times / week	2 times / week	One time / week
Duration	Approx. 5–10 min	Approx. 30 min	Approx. 10 min	Approx. 20 min	Integrated to other exercises
Assessment	Shortness of breath	SPPB [28, 56], RPE [36]	ROM	Time (s), observation	Task accomplishment

*IADL* Instrumental Activities of Daily Living, *ROM* Range of motion, *RPE* Rating of Perceived Exertion (scale 6 to 20), *s* second(s), *SPPB* Short Physical Performance Battery

#### Exercises for muscle strength, power and endurance

The goal is to enhance the participant’s muscle strength, power and endurance, especially in lower limbs, in order to improve postural balance, ability to walk, and functional capacity. Physiotherapy starts with a 2–3-week orientation period based on the Otago exercise program [31]. Strength training is progressive, and follows a cycle where 8-week periods of strength, power and endurance exercises alternate during the intervention year. The intensity goal of strength exercises is 60–80% from the person’s maximal strength of the trained muscle [32–34]. Sets per muscle vary from 2 to 5, and repetitions per set vary from 3 to 12. Muscle power exercises are performed with low to moderate intensity (20–60%) [32], and with high velocity of movement. In power exercises approximately 3 sets and repetitions from 4 to 10 are used [35]. Endurance exercises consist of at least 12 and up to 15–30 repetitions per set, and 2–3 sets per muscle, and the intensity is 20–60% from the person’s maximal strength of the trained muscle [34].

Strength training is individually tailored, and training sets and repetitions are modified according to the participant’s performance [32], health status, and perceived exertion rated by the Borg Rating of Perceived Exertion Scale (RPE, scale 6 to 20) [36] during every session. Progression is achieved by adding resistance with extra weights, such as ankle weights, weight vests, kettlebells and dumbbells, and modifying the sets and repetitions during 12 months.

#### Balance and flexibility exercises

The goal for balance exercises is to enhance the participant’s functional capacity and ability to walk in order to prevent falls. Balance training begins with the Otago exercise program [31], and later on functional exercises are used. The goal for flexibility exercises is to enhance the participant’s range of motion especially in ankle joints and in large joints to maintain activities of daily living. Dynamic flexibility exercises are performed in every physiotherapy session as warm-up exercises or combined with functional exercises.

#### Functional exercises

Functional exercises, such as climbing stairs, chair rise, and walking outside are used to train muscle strength and endurance. Activities of daily living, such as washing dishes, preparing meals, doing laundry or cleaning up are used to train flexibility and balance abilities. Functional exercises are more effective than resistance exercises to improve functional task performance [37].

#### Counselling on physical activity and nutrition

The physiotherapist encourages the participant to exercise on their own, and if possible to take part in the exercise groups organized by municipalities or by third sector organizations. Brief nutritional counselling by the physiotherapist is based on the MNA test [38] and national nutritional guidelines. The main goal of guidance is to reverse possible malnutrition, and ensure sufficient protein intake to prevent weight loss and sarcopenia. Oral nutritional supplements are recommended if necessary.

### Usual care

The participants in the usual care arm continue to live their life “as usual”. They can get any social or health care services that they may need during the 24 months they participate in the study.

### Statistical analyses

The statistical power calculations are based on the hypothesis that the persons with hip fracture assigned to the physiotherapy arm will live at home for six months (180 days) longer than those in the control arm when assessed at 24 months. Our calculations are based on the Finnish PERFECT (PERFormance, Effectiveness and Cost of Treatment episodes) data on hip fractures [39], in which data are available on the proportion of patients living at home 1 year after the fracture (in 2005). To detect a difference of 180 days between the arms, when the type I error is set at 0.05 and the statistical power at 0.8, a sample size of 91 persons in each arm is needed. To allow for discontinuation (estimated as 15% of the participants) and death of patients (20%) during our study period of 2 years, our targeted sample is 300 patients. As to the power calculations of patients with signs of frailty, there are no previous data on the duration of living at home. Therefore we use the same power calculations as for patients with hip fracture. However, the mortality of frail patients is assumed to be lower than that of hip fracture patients.

Frequencies, means and standard deviations will be used to describe background variables of the participants. Differences between the physiotherapy and usual care arm at baseline will be tested by chi-squared test or Fisher exact test for categorical variables, and by t-test or bootstrap type test for continuous variables as appropriate. Analyses will be carried out according to intention to treat. Repeated data will be analyzed using generalized estimating equations (GEE) models with appropriate distribution and link function. In the case of violation of the assumptions (e.g. non-normality), a bootstrap-type test will be used. The normality of the variables will be tested by using the Shapiro-Wilk W test. Incidence rates with 95% confidence intervals (CI) will be calculated assuming a Poisson distribution. Crude and standard estimates of incidence rate ratios (IRR) will be calculated using Poisson regression models, or negative binomial regression models when appropriate. Generalized linear regression model with log link and gamma variance functions will be estimated for social and health service use and costs. Variance function will be selected based on Park test and Akaike’s information criterion. Mortality and its risk factors will be assessed with Cox proportional hazard regression models. Analyses will be performed using IBM SPSS statistics 24 software.

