### Assessments

Previously validated methods for data collection are used in HIPFRA study. Information about the main outcome, duration of living at home, is retrieved from the electronic health records (EHR) of Eksote. The duration of living at home is defined as number of days lived at home during 24 months. Days spent in hospital or in institutional care reduces the number of days lived at home. Change to reside permanently in institutional care or death (within 24 months) are defined as end points.

Interviews, questionnaires, measurements and register information are used to collect data for secondary outcomes. Measurements and interviews based on structured questionnaires are performed at baseline, and after 3, 6, and 12 months at the participant’s home by the study physiotherapist or the study nurse, who are not blinded to randomization. The visit lasts approximately for one and half hours. Before the baseline assessment the participant signs a written informed consent. Before visits the participants are mailed self-reported questionnaires. Register information (for 0–24 months) on the use and costs of social and health care services, medication and mortality will be retrieved from Eksote EHR, the Population Register Centre, and the registers of the Social Insurance Institution (for 0–24 months). Assessment methods of outcomes and other parameters, and the assessment schedule during 24 months are presented in Table 1.

**Table 1 Tab1:** Outcomes, assessment methods and schedule

Outcomes	Parameters and measures [reference]	Scale	Assessment method	Assessment time points (months from the beginning)				
				0	3	6	12	24
Primary outcome	Duration of living at home (days) during 24 months	1–730	Register information					x
Secondary outcomes								
Functional capacity	Instrumental Activities of Daily Living (IADL) [54]	8-31	Interview based on a structured questionnaire	x	x	x	x	
	Functional Independence Measure (FIM) [55]	18–126	Interview based on a structured questionnaire	x	x	x	x	
	Short Physical Performance Battery (SPPB) [28, 56]	0–12	Measurement	x	x	x	x	
	Grip strength (Saehan dynamometer, model Sh5001, South Korea) [57]		Measurement	x	x	x	x	
Frailty status	Fried et al.’s frailty criteria (modified) [1]	0–5	Interview based on a structured questionnaire and measurement	x			x	
Quality-of-life	Health-related quality-of-life (HRQoL) (15D©) [58, 59]	15–75	Self-reported questionnaire	x	x	x	x	

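### The 91-per-arm figure does not fit a comparison of mean days at home: it implies a standard deviation of about 431 days, and a 1–730-day outcome allows at most 364.5

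*Protocol article*

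**What the plan says.** The Assessments section of the protocol article fixes the primary outcome: "The duration of living at home is defined as number of days lived at home during 24 months". Table 1 gives its scale as 1–730 and takes it from registers at 24 months.

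The Statistical analyses section builds the sample size on hip fracture patients in the physiotherapy arm living at home 180 days "longer than those in the control arm when assessed at 24 months". With alpha 0.05 and power 0.8 for that gap, it concludes that "a sample size of 91 persons in each arm is needed". No standard deviation, event rate or test is given for this step. The one source described is a national hip fracture data set in which "data are available on the proportion of patients living at home 1 year after the fracture".

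The figure is then raised to 300 per patient group: "To allow for discontinuation (estimated as 15% of the participants) and death of patients (20%) during our study period of 2 years". The frailty group reuses the same calculation because no earlier data on the outcome exist for it.

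**The concern.** A difference, an error rate, a power and a sample size together fix the standard deviation that a comparison of means must have assumed. A bounded outcome also has a largest possible standard deviation. If the first exceeds the second, the printed figures cannot all describe the same comparison, and no input held in a fuller document could reconcile them for a test of means.

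What is at stake is interpretation. The same sentence supports both randomised comparisons, 600 participants in all. A reader will take 180 days as the difference that the trial has 80% power to find, and will judge a null or modest result against that benchmark. If the benchmark does not belong to the outcome, that judgement is misplaced.

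**Working it through.** **Inputs from the protocol article.** Difference 180 days; type I error 0.05; power 0.8; 91 per arm, equal allocation (Statistical analyses). Outcome range 1 to 730 days (Table 1). Sidedness and test are not stated; a two-sided two-sample comparison of means is assumed and alternatives are tried in step 5.

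**1. Standard deviation implied by 91 per arm.**
- Normal approximation: n = 2(z₀.₉₇₅ + z₀.₈)² SD² / 180², so SD = 180 × √(91/2) / 2.8016 = 433 days.
- t-test: the standardised difference detectable with 91 per arm is 0.4176, so SD = 180 / 0.4176 = 431 days.
- Rounding of n does not matter: 88 to 94 per arm implies 424 to 438 days.

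**2. Largest standard deviation that the scale allows.**
- A variable confined to 1–730 has SD ≤ (730 − 1)/2 = 364.5 days, reached only if half the patients score 1 and half score 730.
- For a given mean m, the variance is at most (m − 1)(730 − m). With arm means 180 days apart, the average of the two bounds is largest when the means lie symmetrically at 275.5 and 455.5. Each arm's bound is then 274.5 × 454.5 = 124,760, so the common SD is at most √124,760 = 353 days.

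The plan's 91 is therefore not reproduced for a comparison of means by any SD that the scale permits.

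**3. Size needed, and power with 91 per arm, for 180 days (t-test, two-sided 0.05).**

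| SD (days) | Status | Needed per arm, power 0.8 | Power with 91 per arm |
|---|---|---|---|
| 431 | implied by the plan; not possible on 1–730 | 91 | 0.80 |
| 364.5 | absolute limit | 66 | 0.91 |
| 353 | limit with means 180 days apart | 62 | 0.93 |
| 300 | illustrative assumption | 45 | 0.98 |
| 250 | illustrative assumption | 32 | 0.998 |

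**4. Difference detectable at 80% power, at the limiting SD of 353.**
- 91 per arm: 0.4176 × 353.2 = 147 days.
- 150 per arm: the detectable standardised difference is 0.3245, and 0.3245 × 353.2 = 115 days.

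A smaller SD lowers both figures.

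**5. Other routes to 91.**
- One-sided testing implies an SD of 486 days, further from the limit. A two-sided level of 0.025, which the article does not state, would still imply 391.
- Treating the outcome as all-or-nothing at 1 or 730 needs at most 64 per arm, or 72 with continuity correction.
- A log-rank test with a 180-day difference in restricted mean over 730 days, under exponential times, needs about 12 to 33 per arm.
- 91 does appear for other quantities: two proportions such as 60% v 79%, or an unbounded time-to-event model with a 180-day difference in median or mean and a 1-year proportion of roughly 30–43%.

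**6. Enrolment.** Applying the stated losses to 91 gives 91/(1 − 0.35) = 140 per arm, or 91/(0.85 × 0.80) = 134 per arm, against 150 planned.

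**The case against.** The strongest reply is that the article names no test, so the argument from the standard deviation binds only a comparison of means. This stands. A reader might infer that no distribution of this outcome could make 91 right, and that would go too far. A contrived case shows why: put 40%, 21% and 39% of controls at days 1, 700 and 730, against 15%, 34% and 51% in the physiotherapy arm. The means differ by about 178 days and the probability of superiority is 0.61. A rank test with tie correction then needs about 90 per arm. The Statistical analyses section names no rank test, and the pattern is artificial, but the limit has to be stated for means. The 91% power floor likewise assumes a t-test.

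The Assessments section also calls permanent institutional care and death end points, and a 1-year proportion is a natural input to a time-to-event calculation. The authors may have computed 91 that way. This is plausible but unproven, and it would confirm that 91 belongs to something other than the defined count of days.

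Thirdly, a condensed article may leave its standard deviation and formula to the full protocol. That is right, and their absence is not the point here. The point is that the printed figures conflict for a comparison of means.

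Finally, the error is conservative: 91 per arm exceeds what a t-test for 180 days needs, and 300 per group covers the stated losses. This stands too, and it limits the severity.

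**Conclusion.** The point holds for a comparison of mean days at home. With 91 per arm, 180 days, two-sided 0.05 and power 0.8, the implied SD is about 431 days, against a limit of 364.5, or about 353 once the 180-day difference is imposed. The limits need no outside data; they rest on the 1–730 scale, and the implied SD rests on a two-sample test of means. Since the only named source is a 1-year proportion, 91 seems to belong to another quantity, but its origin is conjecture.

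Two stronger readings are tempting and not supported. One is that the trial is underpowered for 180 days: the reverse is true, with at least 91% power for 91 per arm in a t-test. The other is that the design can be credited with detecting a specific, much smaller difference. An SD of 220–255 days would give about 71–83 days with 150 per arm, but that SD rests on assumed event timing, assumed hospital days and an institutionalisation rate that the plan does not adopt, and on all 150 per arm being analysed. What the article itself supports is the figure at the limit: about 147 days with 91 per arm and 115 days with 150.

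This is a wrong stated figure that should be corrected. It does not call the design or the enrolment target into question.

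**What to change.** Revise the sample-size paragraph and keep enrolment at 300 per patient group.

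- State which quantity, test and inputs produced 91.
- If it came from a comparison of proportions or a time-to-event calculation, say so, and remove the claim that it is the size for a 180-day difference at power 0.8.
- Restate the power, or the detectable difference, for days lived at home, using an SD with a stated source and no greater than about 353 days, for the number expected to be analysed. Since the frailty group borrows the calculation and is assumed to have lower mortality, say whether the same SD is meant to apply to it.
- If an SD of 220–255 days and the resulting 71–83 days are shown at all, present them as an illustration under declared assumptions, not as the replacement figure.

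The cost is one recalculation and the rewording of one paragraph. No extra patients and no change to design or analysis are needed.

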### Outcomes of the study

The primary outcome is duration of living at home. The secondary outcomes are functional capacity, frailty status, health-related quality-of-life, and number of falls, use and costs of social and health care services, and mortality.

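### The confidence intervals for incidence rates are fixed as Poisson with no allowance for overdispersion, so arm-specific fall rates would be reported too precisely if falls cluster within people

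*Protocol article*

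**What the plan says.** The Statistical analyses section of the protocol article treats rates and rate ratios in two adjacent sentences. For the rates: "Incidence rates with 95% confidence intervals (CI) will be calculated assuming a Poisson distribution". For the ratios, the estimates "will be calculated using Poisson regression models, or negative binomial regression models when appropriate". The first sentence offers one distribution and the second offers two. Neither names an outcome.

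The outcomes section lists the candidates: "The secondary outcomes are functional capacity, frailty status, health-related quality-of-life, and number of falls", followed by use and costs of services, and mortality. Elsewhere in Statistical analyses, service use and costs go to a generalized linear model with log link and gamma variance, and mortality goes to Cox regression. Number of falls is the one recurrent event count with no named model of its own. Table 1 has falls collected by interview, and the Assessments section says interviews are "performed at baseline, and after 3, 6, and 12 months at the participant’s home".

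**The concern.** A Poisson interval for a rate treats all events in an arm as independent and everyone as sharing one underlying rate. Falls rarely behave like that. The eligibility criteria admit people with a single frailty point as well as those with several, walkers with and without aids, and MMSE scores from 17 (frailty group) or 12 (hip fracture group) upward. Any variation between people in the underlying rate pushes the variance of the counts above the mean, and the Poisson interval is then too short.

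The article foresees this for the ratio, where it allows a negative binomial model, but not for the rates that form the ratio. If that model were used for falls, the report would show a ratio that allows for the extra variance beside two arm rates that ignore it. At stake is the stated precision of the fall rates in each arm. Falls are a secondary outcome, and their prevention is an explicit aim of the balance training.

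**Working it through.** **Which figures exist.** The article gives no fall rate, dispersion or interval width, so there is no figure of its own to reproduce. The rates and dispersions below are assumptions and are shown as ranges.

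**Formula.** Let μ be the mean number of falls per person-year and k the negative binomial dispersion. The variance of one person's yearly count is μ(1 + kμ), against μ under Poisson. Hence:

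- variance ratio = 1 + kμ
- ratio of true to reported standard error = √(1 + kμ)
- approximate true coverage of a nominal 95% interval = 2Φ(1.96/√(1 + kμ)) − 1

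| Assumed μ | Assumed k | Variance ratio | SE ratio | Coverage |
|---|---|---|---|---|
| 1 | 0.5 | 1 + 0.5 × 1 = 1.5 | 1.22 | 89% |
| 1.5 | 1.0 | 1 + 1.0 × 1.5 = 2.5 | 1.58 | 78% |
| 1.5 | 1.5 | 1 + 1.5 × 1.5 = 3.25 | 1.80 | 72% |

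Sample size cancels from these ratios, so a larger trial would not restore coverage.

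**Check by simulation.** Each patient group has a target of 300 ("our targeted sample is 300 patients"). Equal allocation is assumed, since the ratio is not stated, which gives 150 per arm. Each person is taken to contribute one full year. Exact (chi-square) Poisson intervals were computed for one arm's rate in 20,000 simulated data sets per setting. Half-widths are 1.96 × √(μ(1 + kμ)/150).

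| μ | k | Half-width, Poisson | Half-width, negative binomial | Simulated coverage of the Poisson interval |
|---|---|---|---|---|
| 1 | 0 | 0.160 | 0.160 | about 95% |
| 1 | 0.5 | 0.160 | 0.196 | 90% |
| 1 | 1 | 0.160 | 0.226 | 84% |
| 1 | 2 | 0.160 | 0.277 | 75% |

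At μ = 1 the simulation agrees with the formula to within about one percentage point. Over a wider range (μ from 0.5 to 3, k from 0.5 to 3) the correct interval is 1.12 to 3.16 times as wide as the Poisson one, and coverage runs from 92% down to 47%. With no overdispersion the Poisson interval is correct.

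**The case against.** The strongest reply is that arms are compared through the rate ratio, and there the article already provides for overdispersion. That stands. A reader might infer that the fall comparison itself has an inflated false-positive rate. At the variance ratios above it would be about 11% to 28% instead of 5% (100% minus coverage), but only if Poisson were used for the ratio despite overdispersion. The article does not fix that, and the criterion for choosing between the two models is detail that a condensed article may leave to the full plan.

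Two further extensions are tempting and not supported. Nothing applies a Poisson interval to days lived at home; the article defines that outcome as a number of days and never calls it an incidence rate. Service use and costs have their own gamma model, with the variance function selected by Park test and Akaike's criterion.

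It can also be said that the link to falls is inferred. The sentence could be meant for events that happen once, such as death or permanent institutional care, where repeated events in one person do not arise. Falls, being recorded at several visits, might also come under another provision: "Repeated data will be analyzed using generalized estimating equations (GEE) models with appropriate distribution and link function". Both readings are possible. Neither removes the rule as written: any fall rate reported with an interval would get a Poisson one, and falls remain the only recurrent count among the secondary outcomes without a named model.

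Finally, the size rests wholly on assumed rates and dispersions. That stands too, and it is why the result is given as a range and made conditional on clustering.

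**Conclusion.** The point holds for the arm-specific rate intervals. The article fixes them as Poisson while accepting, one sentence later, that Poisson may not suit the same kind of data. This is a stated rule, so it is not a matter of detail left to a plan that is not shown. Applied to falls that cluster within people, as is expected here, it gives intervals that are too narrow: reported standard errors would need multiplying by about 1.2 to 1.8, and true coverage would be about 89% down to 72%. This assumes 1 to 1.5 falls per person-year, a dispersion of 0.5 to 1.5, and falls as the outcome meant. If counts prove close to Poisson, the intervals are sound.

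Severity is minor. The intervals describe each arm's rate for a secondary outcome; the between-arm ratio is not tied to Poisson.

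**What to change.** Replace the sentence on incidence rates with one stating that fall rates in each arm, their ratio and all 95% intervals come from the same method, chosen in advance and robust to overdispersion: a negative binomial model, or a participant-level robust or bootstrap variance. Use the log of person-time under observation for falls as offset, running up to 12 months and ending earlier at death or discontinuation. Time alive would be the wrong exposure. Falls are ascertained by interview only to 12 months and the article expects 15% of participants to discontinue, so unobserved time would count as time without falls and pull the rates down.

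The cost is one sentence and wider rate intervals, by about 1.2 to 1.8 times under the assumed values. If the counts turn out near Poisson, almost nothing is lost.
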